### 2.2. Study Settings

According to our pilot study, we evaluate the time required by the participant at about 15 min per phase.

For the first phase, investigators will assess the Karasek’s questionnaire, food intake questionnaire, Maslach Burnout Inventory, and Hospital Anxiety Depression Scale (HAD) among Emergency health care workers at the beginning of the control day (around 8:30 am). A sample of saliva in an Eppendorf will be recovered at the same time. Saliva collection will be brought in a cooler to the Institute of Occupational Medicine of Clermont-Ferrand by the end of the day. The samples will be stored at −80 °C. The experimenter will also deliver a pre-stamped envelope for the return of 2 Eppendorf tubes (saliva collection) and questionnaires at the end of the day.

Considering the difficulties of obtaining homogenous planning with all emergency providers, the time passed between the first and the second phase will not be the same between all providers. However, the 2 phases need to be separated by at least 1 week.

For the second phase, investigators will assess the same questionnaires with the saliva collection at the beginning and the end of a 24-hour or 14-hour nightwork session (up to 1 week later). This will permit the evaluation of the relationships between modifications in questionnaire answers and biological responses by comparing results during a control day versus results at the end of a work session, including a nightshift.

The third phase of the SEEK protocol is a longitudinal follow-up. This study design will be reproduced every 5 years in all Emergency Departments. If possible, i.e., if they are already in the same Emergency Department, we will follow-up on the initial cohort. We choose a follow-up of 5 years because it corresponds to the residency program duration in Emergency Medicine in France. We will program 4 sessions for a total of 20 years.

### 2.3. Ethics and Dissemination

A French Ethics committee (Comité de Protection de Personnes Sud-Est I, CHU Saint-Etienne) approved this study protocol on 3 November 2014, with reference DC-2014-2151. This protocol was registered in ClinicalTrials under the identification NCT02401607.

The results of questionnaires will be coded and managed through ReDCap© software with pseudonymous codification.

### 2.4. Eligibility Criteria

To fulfill the inclusion criteria, every health care worker will need to over 18 years of age and working in an Emergency Department in France. No requirement of experience is necessary. Healthcare workers will be excluded for refusal of participation, intercurrent pathology with hormones disabilities, impracticability to take the follow-up, psychopathology with depression or anxiety, taking any drugs that modulate inflammation or hormones levels, and pregnancy.

### 2.5. Recruitment Process

During each part of the study, 120 emergency health care workers will be recruited as participants. During the recruitment phase, all emergency health care workers will individually receive an information letter attached by email. Acceptance or refusal will be given by mail to avoid any subordination effect between the experimenter and the recruited. If they agree, they will have 8 days to sign the consent form to participate in the study. For privacy purposes, the question about their medical history will not be asked by email. Instead, a list of non-inclusion criteria will be given in the information letter. Thus, if any exclusion criteria are present, they can refuse participation without any need for further explanation.

### 2.6. Outcomes

The primary outcome is the participants’ score with respect to the Karasek questionnaire in terms of the 3 dimensions, namely psychological demands, decision latitude, and social support at work.

Secondary outcomes are different biological measures of stress (cortisol concentrations, DHEA-S, salivary IgA, and lysozymes); some psychological questionnaires (see below for details), namely the Maslach Burnout Inventory, the Hospital Anxiety and Depression Scale; and some question about stress (at home, in life, and at work), about sleep quality, and about mental and physical fatigue. Lastly, we will assess food intake using a quantitative and qualitative questionnaire.

## 3. Results

### 3.1. Justification of the Sample Size

The number of subjects required justification is based on the ability to recruit participants, namely 120 subjects. Previous studies have shown an acceptance rate above 80% in the emergency health care workers’ population; power estimates will be provided based on 100 subjects included. In addition to the expected variability, this type of study can have a fixed margin of error on the estimated sample size (reliability of the sample). Referring to the data of our pilot study, the Karasek questionnaire found low decision latitude (59.67 ± 6.44, 6% higher than 71), a significant psychological burden (29.39 ± 4.07; 94% greater than 20), and high social support (29.94 ± 3.21, 100% above 24), meaning that with at least 100 subjects considered, the error margin will be very satisfying that is respectively ±1.25, ±0.8 and ±0.63. If we consider the different dimensions score as categorical (<> 71 <> 20 and <> 24), accuracy will be ±5% with n = 100.

Furthermore, simulations on secondary objectives can complete this justification. To see a change in the emergency health care workers’ work perception during a control day versus the results at the end of a nightshift, 100 subjects will show minimum differences of the order of 2.35, 1.48, and 1.17 for decision latitude dimensions, psychological demand, and social support, with a type 1 error risk of 5%, a power of 95% and a correlation coefficient of 0.5 (matched condition).

With 100 subjects, and given the assumptions described above, 5 predictors can be explored to identify factors that explain emergency work perception for a power greater than 80% [47].

### 3.2. Data Collection and Management

Seven questionnaires will be presented to every participant. All psychological assessments will be self-reported.

#### 3.2.1. Karasek Questionnaire

Karasek’s questionnaire [21] was French-validated by Brisson et al. in 1998 [48]. The questionnaire includes 26 items measuring the 2 burnout sources: The decision latitude, with 9 items, and psychological job demands, with 9 items. For each item, the subject is asked to respond using a 4-level Likert-type scale. Thus, a high score in the first dimension means that the worker acts autonomously and is less exposed to burnout. Meanwhile, a high score in the second dimension implies that the subject is under a heavy workload, leading to severe psychological stress. Social support, explored by 8 items, acts as a burnout modulator: High social support helps to better tolerate situations linked with burnout emergence. The analysis is based on the median of each factor.

The psychological demand is calculated with the following formula: Q10 + Q11 + Q12 + (5 − Q13) + Q14 + Q15 + Q16 + Q17 + Q18. A score below 20 reflects a low psychological demand. The decision latitude is calculated with the following formula: 4 × Q4 + 4 × (5 − Q6) + 4 × Q8 + 2 × (5 − Q2) + 2 × Q5 + 2 × Q7 +2 × Q1 + 2 × Q3 + 2 × Q9. A score below 71 reflects low decision latitude. Finally, the social support is calculated with the following formula: Q19 + Q20 + Q21 + Q22 + Q23 + Q24 + Q25 + Q26. A score below 24 reflects low social support [22]. In a previous study performed by our team, the Cronbach’s alphas for job demands, job control, and social support were 0.58, 0.99, and 0.99, respectively [49].

In summary, the Karasek questionnaire postulates that a work situation generates stress if it combines high psychological demands, low decision latitude, and low social support from the work team or hierarchy. By combining autonomy and demand, 4 broad categories are defined:−Relaxed work: Low demand, high autonomy−Passive work: Low demand, low autonomy−Active work: High demand, high autonomy−Stressed, tense work: High demand, low autonomy

#### 3.2.2. Maslach Burnout Inventory (MBI) Scale

The MBI scale [50] evaluates 3 different components, giving a burnout evaluation for each component: Emotional exhaustion, depersonalization, and personal accomplishment. Dion and Tessier made a French-translated version of the MBI scale [51]. The scale is composed of 22 items measuring 3 different burnout dimensions: Emotional exhaustion, depersonalization, and personal accomplishment. For each item, the subject is asked to indicate using a 7-point scale the occurrence frequency of the feeling corresponding to a state. Thus, a high score in the first 2 subscales reveals a burnout state. In contrast, a high subscale score on achievement means that the subject feels fulfilled professionally (the achievement subscale is inverted). In a previous study performed by our team in a similar population, analysis of internal consistency yielded a Cronbach’s alpha of 0.785, indicating scale reliability [52].

#### 3.2.3. Hospital Anxiety and Depression Scale (HAD) Scale

Zigmond & Snaith’s (1983) HAD Scale explores anxiety and depression [53]. It was translated into French by Lépine in 2000 [54]. The scale is composed of 7 items exploring anxiety symptoms, and 7 others exploring depressive symptoms. Each item is given on a 4 degrees-of-severity scale. Anxiety and depression score ranges from 0 to 21. The generally admitted pathological thresholds score is 8. In a previous study performed by our team in a similar population, the Cronbach’s alphas for the components of depression and anxiety were 0.82 and 0.79, respectively [49].

#### 3.2.4. Sociodemographic Report

A unique questionnaire will be used to collect sociodemographic data such as age, sex, weight, height, and marital status. Information about medical history, drugs, and pregnancy (if female) will be collected. A second part of the questionnaire will assess the physical activity (number of hours per week and intensity) and sleep of every health care worker (number of hours and quality assess by a visual analogic scale from worst to best). Others visual analogic scales will assess stress and mental and physical tiredness.

#### 3.2.5. Place of Work

Information about the Emergency Department and hospital such as type of hospital (university or not), number of patients every year, and type of patients (adult, kids, both) will be collected.

#### 3.2.6. Occupational Characteristics

These include seniority (within the hospital, within the Emergency Department, and as an emergency occupation), current position (physician, internship or externship student, nurses, caregivers, cleaners, secretary, hospital porter, other), and type of contract (permanent or temporary). For physicians, these characteristics also include the type of emergency diploma or initial specialty and more details on contracts (professors, senior lecturer, hospital practitioner, assistant).

#### 3.2.7. Food Intake

To study the qualitative and quantitative food intake of emergency health care workers, participants will be given a questionnaire. Three timepoints will be examined—before, during, and after nightshift—and compared to a control day. We will ask participants to complete a 3-day dietary recall that will be explained and detailed to them by a member of the investigation team. We will ask to participants to indicate all the details regarding the food ingested at each meal and in-between meals as precisely as possible. A specialized dietician will provide details in the diary as well as some guidance on how to complete it. Subsequently, the diaries will be reviewed with the participants and the dietitian during a 45-min interview [55]. All data will be pooled and translated in kcal., and the quantity of lipids, carbohydrates, and proteins will be evaluated using the software Nutrilog^®^.

#### 3.2.8. Biological Samples

Several assays will be performed on the saliva sample. Biological analyses will be conducted by the Institute of Occupational Medicine of the Medical School of Clermont-Ferrand. We will measure salivary cortisol concentrations, DHEA-S, sIgA, and lysozymes. These parameters have been reported in the literature as correlated with the level of stress or workload. Only steroids (cortisol and DHEAS) with good stability will be measured in both samples. Peptides (sIgA and lysozyme) will be measured only during the dayshift (control). The samples made after the work session will be sent by post, which does not guarantee sIgA and lysozyme preservation.

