### 3.3. Data Analysis

Continuous variables will be presented as mean and standard-deviation or median and interquartile range according to the statistical distribution. The normality assumption will be assessed using Shapiro–Wilk test. Categorical variables will be expressed as numbers and associate percentage. The primary analysis will be mainly descriptive and will define the perception scores of emergency physicians work according to the Karasek questionnaire for each dimension composing the score (decision latitude, psychological demands, and social support), as quantitative and categorical variable. A correlation matrix analysis on quantitative variables (i.e., Karasek questionnaire and other psychological questionnaires) will be conducted using Pearson or Spearman correlation coefficients, in addition to principal component analysis (PCA). The Karasek questionnaire score’s evolution, obtained for each dimension, will be tested with a paired two-sample Student’s test, or nonparametric Wilcoxon test if necessary. Linear regression models and random-effects models will complete these analyses. These models will permit, with multivariable analyses and covariates’ introduction, to seek possible explanatory factors of the Karasek score (a dayshift (control) versus the end of 24 h or shift) and its evolution. The same statistical analysis plan will be used for continuous parameters collected after the dayshift (control) and after the 24-h shift (e.g., all biological samples). For categorical variables, Stuart-Maxwell test will be used. The comparisons for quantitative parameters (e.g., biological data, questionnaires’ scores) will be based on Student’s *t*-test or nonparametric Mann–Whitney test. The comparisons involving categorical parameters (gender, seniority) will be made with the Chi-squared test or Fisher’s exact test. All statistical analyses will be performed as two-sided tests, with a *p* < 0.05 considered as significant. Statistical analyses will be performed using the Stata software (version 16, StataCorp, College Station, TX, USA).

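### On the most natural reading, control-day saliva is cooled and post-shift saliva is posted, so a handling effect on cortisol or DHEA-S cannot be separated from the nightshift effect

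*Protocol article*

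**What the plan says.** Section 2.2 of the protocol article (Study Settings) describes the control-day sample, taken at about 8:30 am: "Saliva collection will be brought in a cooler to the Institute of Occupational Medicine of Clermont-Ferrand by the end of the day". It adds: "The samples will be stored at −80 °C".

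The same phase 1 paragraph says that the experimenter will "deliver a pre-stamped envelope for the return of 2 Eppendorf tubes (saliva collection) and questionnaires at the end of the day". It does not say which two tubes these are.

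For phase 2, section 2.2 schedules saliva at the start and at the finish of the night session. It gives the purpose as "comparing results during a control day versus results at the end of a work session, including a nightshift".

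Section 3.2.8 (Biological Samples) fixes what is assayed: "Only steroids (cortisol and DHEAS) with good stability will be measured in both samples". The two peptides are assayed on the control day only, for this reason: "The samples made after the work session will be sent by post, which does not guarantee sIgA and lysozyme preservation".

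Section 3.3 (Data Analysis) carries the paired and regression analysis over to the biomarkers: "The same statistical analysis plan will be used for continuous parameters collected after the dayshift (control) and after the 24-h shift". The Potential Limitations section names uneven shift workload as a source of biological variation. It does not mention sample handling.

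**The concern.** In a paired comparison each participant serves as their own control, but this protects only against factors that stay the same across the two occasions. If every control tube is cooled and every post-shift tube is posted, transport changes together with the condition under study. The mean paired difference then estimates the nightshift effect plus any postal effect. A covariate or random effect cannot split the two, because in these data they never vary separately.

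What is at stake is the reading of the planned control-versus-post-shift change in cortisol and DHEA-S. A modest systematic change in the posted tubes could create an apparent stress response or mask a real one, and nothing described in the article would reveal it. The design is to be repeated at four sessions over 20 years, so an unmatched route would recur at each.

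**Working it through.** **Step 1. Routes side by side**

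| Tube | Route stated | Where |
|---|---|---|
| Control day, about 8:30 am | Cooler to the laboratory that day; −80 °C storage | 2.2 |
| Start of night session | Not stated | 2.2 |
| End of night session | Post; no temperature or transit time given | 3.2.8 |
| Two tubes in the envelope | Post; tubes not identified | 2.2 |

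The reason given for assaying peptides on the control day only is that post-shift tubes are posted. That makes sense only if the control tube used for the peptides is not posted. The planned contrast, control day against end of session, therefore most naturally sets a cooled tube against a posted one.

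**Step 2. Check of the paired formula against the protocol's own figures**

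Section 3.1 gives no detectable difference for cortisol or DHEA-S. It does give differences for the Karasek dimensions: n = 100, correlation r = 0.5, two-sided alpha 0.05, power 95%, with pilot SDs 6.44, 4.07 and 3.21.

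- SD of the paired difference = SD × √(2(1 − r)) = SD × √(2 × 0.5) = SD.
- Normal approximation for decision latitude: (1.960 + 1.645) × 6.44 / √100 = 2.322.
- Exact, by the noncentral t: 2.344, 1.482 and 1.169, against the stated 2.35, 1.48 and 1.17.

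The protocol's figures are reproduced, so the same formula is used below.

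**Step 3. Illustration for a handling shift with no nightshift effect**

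Assumptions: 100 pairs; r = 0.5, which section 3.1 states for the Karasek scores and is borrowed here for the biomarkers; and a handling shift b, in units of the SD of one measurement, which no document supplies.

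- SE of the mean difference = SD × √(2 × 0.5) / √100 = 0.1 SD.
- Noncentrality = b / 0.1. A shift of 0.1 SD is 1 SE and a shift of 0.2 SD is 2 SE.
- Chance of a significant result = probability that a noncentral t on 99 degrees of freedom exceeds the two-sided 5% limits.

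| Assumed shift (SD) | r = 0.3 | r = 0.5 | r = 0.7 |
|---|---|---|---|
| 0 | 5% | 5% | 5% |
| 0.05 | 7% | 8% | 10% |
| 0.1 | 13% | 17% | 25% |
| 0.2 | 39% | 51% | 73% |
| 0.3 | 71% | 84% | 97% |

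With other correlations the SE multiplier changes: √(2 × 0.7) = 1.18 at r = 0.3 and √(2 × 0.3) = 0.77 at r = 0.7.

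The table shows how sensitive the comparison would be to a given shift. It does not show that a shift exists.

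**The case against.** The best case for the protocol has three parts.

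**The protocol saw the problem and responded.** It withdrew the two analytes whose preservation the post could not assure and kept only steroids it regards as stable. A reader might infer that the post is known to degrade the samples. The text says only that preservation of the peptides is not guaranteed, and nothing in it shows loss of cortisol or DHEA-S. This part stands, and it makes the concern conditional. It does not remove it, because the claim of stability comes without transit conditions or supporting data. The half-life in the Background concerns DHEA and is used to argue for steady levels through the day, not for stability in a posted tube.

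**The alignment of route and condition is not certain.** The two-tube envelope appears in the control-day paragraph, and section 3.3 speaks of parameters collected after the dayshift. Together these could mean that end-of-control-day tubes are also posted. The envelope could instead hold the start- and end-of-session tubes. Either would supply a like-for-like comparator. This stands as an ambiguity that the sponsor must resolve. One should not assert that handling and condition coincide in every participant.

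**Other shift contrasts exist.** A reader might take the control-to-post-shift change as the only shift response available from saliva. Section 2.2 also takes saliva at the start of the session, so a within-session change can be derived. However, the stated contrast is control day against end of session, and section 3.2.8 speaks of two samples, not three.

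A reader might also see a contradiction between investigators collecting saliva at the session and the tubes then being posted. There is none: one concerns collection, the other transport.

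**Conclusion.** The point holds in a conditional form. On the most natural reading of sections 2.2 and 3.2.8, the planned cortisol and DHEA-S comparison sets a cooled tube against a posted one, and any systematic postal effect would be indistinguishable from the nightshift effect. The article describes no matched handling, and no later analysis could repair this once the samples are taken.

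The size is unknown. Under the assumed 100 pairs and correlation of 0.5, shifts of 0.1 and 0.2 SD would give false nightshift findings about 17% and 51% of the time. At 0.2 SD the range is 39% to 73% for correlations from 0.3 to 0.7. These are illustrations, not estimates of the bias in this study.

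Only secondary biomarker outcomes are touched. The primary Karasek scores are unaffected.

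**What to change.** 1. State in sections 2.2 and 3.2.8 which tubes are posted, including the two in the pre-stamped envelope and the start-of-session tube.
2. Compare cortisol and DHEA-S only between tubes that took the same route. Split the control-day saliva, post one aliquot in the same type of envelope, and use it for the steroid comparison. Keep the cooled aliquot for sIgA and lysozyme.
3. If the start-of-session tube is posted with the end-of-session tube, also report that like-for-like contrast.
4. Optionally, assay both steroids in the cooled control aliquot as well. The posted-minus-cooled difference then measures the handling effect directly.

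The cost is one extra tube, with its postage, per participant and no extra visit. Item 4 adds about 100 assays of each steroid. If control-day tubes are in fact already posted, items 1 and 2 need only a clearer text.

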### 3.3. Data Analysis

Continuous variables will be presented as mean and standard-deviation or median and interquartile range according to the statistical distribution. The normality assumption will be assessed using Shapiro–Wilk test. Categorical variables will be expressed as numbers and associate percentage. The primary analysis will be mainly descriptive and will define the perception scores of emergency physicians work according to the Karasek questionnaire for each dimension composing the score (decision latitude, psychological demands, and social support), as quantitative and categorical variable. A correlation matrix analysis on quantitative variables (i.e., Karasek questionnaire and other psychological questionnaires) will be conducted using Pearson or Spearman correlation coefficients, in addition to principal component analysis (PCA). The Karasek questionnaire score’s evolution, obtained for each dimension, will be tested with a paired two-sample Student’s test, or nonparametric Wilcoxon test if necessary. Linear regression models and random-effects models will complete these analyses. These models will permit, with multivariable analyses and covariates’ introduction, to seek possible explanatory factors of the Karasek score (a dayshift (control) versus the end of 24 h or shift) and its evolution. The same statistical analysis plan will be used for continuous parameters collected after the dayshift (control) and after the 24-h shift (e.g., all biological samples). For categorical variables, Stuart-Maxwell test will be used. The comparisons for quantitative parameters (e.g., biological data, questionnaires’ scores) will be based on Student’s *t*-test or nonparametric Mann–Whitney test. The comparisons involving categorical parameters (gender, seniority) will be made with the Chi-squared test or Fisher’s exact test. All statistical analyses will be performed as two-sided tests, with a *p* < 0.05 considered as significant. Statistical analyses will be performed using the Stata software (version 16, StataCorp, College Station, TX, USA).

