## 4. Discussion

This protocol seems particularly innovative considering the lack of emergency health care workers in the SUMER study. Indeed, those workers are mainly at risk of burnout [4]. Furthermore, and even if it was not the main objective, the recent actuality with the COVID-19 pandemic showed an increase in the workload for emergency health care workers. Indeed, even in the area with low incidence of first wave of COVID [56], overcrowding is increasing in the Emergency Departments [57]. Furthermore, the 20 years of follow-up will make it possible to assess the impact of local (an increase of the number of workers during shifts, change in the food quality and quantity…) and national policy (no more 24-h shifts, security rest after a nightshift) on the well-being of workers. This study will bring important data about emergency health care workers’ work perception and stress. No data on the Karasek questionnaire score currently enable u, to compare Emergency Medicine with other medical specialties. Indeed, the SUMER study did not include any emergency health care workers. The SUMER study [30] conducted in France on 25,000 employees in 2002–2003 found that all confounded professions produced average psychological demand scores of 21.5 for men and 21.8 for women, and average decision latitude scores of 71.9 for men and 68.8 for women. The distribution of these four broad categories was Relaxed 29.2%, Passive 25.2%, Active 25.2%, and Tense 20.4%. The SUMER study can be used to identify the psychological demands and decision latitude mean scores by professional family.

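### The choice between mean and median for the primary Karasek scores is left to a normality test, although the study's precision and its SUMER benchmarks are for means

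*Protocol article*

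**What the plan says.** The primary outcome (2.6) is the Karasek score on psychological demands, decision latitude and social support. Section 3.3 describes its analysis: "The primary analysis will be mainly descriptive and will define the perception scores of emergency physicians work according to the Karasek questionnaire", with each dimension treated both as a quantity and as a category.

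The summary of the quantity is conditional: "Continuous variables will be presented as mean and standard-deviation or median and interquartile range according to the statistical distribution". The next sentence gives the criterion: "The normality assumption will be assessed using Shapiro–Wilk test". The change in each dimension between the control day and the end of the night session is to be tested with a paired Student test, "or nonparametric Wilcoxon test if necessary". Regression and random-effects models are to complete this.

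Section 3.1 justifies 100 subjects by margins of error that are "respectively ±1.25, ±0.8 and ±0.63" for latitude, demand and support. It adds detectable paired differences of 2.35, 1.48 and 1.17. The Discussion quotes SUMER average scores for demand (21.5 men, 21.8 women) and latitude (71.9 men, 68.8 women), and states: "The SUMER study can be used to identify the psychological demands and decision latitude mean scores by professional family".

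**The concern.** The main result is an estimated score per dimension. Its planned precision refers to a mean, and so does its external comparator for two of the three dimensions. The rule in 3.3 does not commit to reporting that mean. It lets the observed distribution choose, and the named tool is a test that reacts at n near 100 to discreteness and ceiling effects in bounded integer scores. Those features do little harm to inference on a mean.

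Two things are at stake. The three dimensions could be summarised differently within one report. The same dimension could also be a mean at one 5-year wave and a median at the next, which weakens the comparison over 20 years that the protocol sets out to make. No precision is stated anywhere for a median.

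**Working it through.** **Inputs.** Pilot mean ± SD (3.1): latitude 59.67 ± 6.44, demand 29.39 ± 4.07, support 29.94 ± 3.21. n = 100 (3.1). Score formulas with 4-level items (3.2.1), coded 1 to 4 as the 5 − Q reversals imply: latitude 24 to 96 in steps of 2, demand 9 to 36, support 8 to 32. Assumed: Shapiro–Wilk at 0.05, and the score shapes, which the documents do not give.

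**1. The stated margins are for means.** Half-width = 1.96 × SD / √n.
- Latitude: 1.96 × 6.44 / 10 = 1.26 (stated 1.25)
- Demand: 1.96 × 4.07 / 10 = 0.80 (stated 0.8)
- Support: 1.96 × 3.21 / 10 = 0.63 (stated 0.63)

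**2. The detectable differences are also for means.** With correlation 0.5 the SD of a paired difference is SD × √(2 × (1 − 0.5)) = SD. The normal approximation at 95% power is (1.96 + 1.645) × SD / 10, which gives 2.32, 1.47 and 1.16. The t-based version gives 2.34, 1.48 and 1.17, against 2.35, 1.48 and 1.17 stated.

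**3. Distance to the ceiling.** Support: (32 − 29.94) / 3.21 = 2.06 / 3.21 = 0.64 SD.

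**4. How often Shapiro–Wilk would reject.** Simulated samples of 100 from a normal with pilot mean and SD, rounded to the score grid and capped at the limits (4,000 runs):
- Latitude: about 22%
- Demand: about 70%
- Support: about 100%

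Capping pulls the simulated support scores to mean 29.4 and SD 2.5, so this shape does not hold the pilot values exactly. Shapes fitted to mean 29.94 and SD 3.21 (beta-binomial, censored normal) also reject in about 100%. The demand figure depends on shape: 13% with rounding but no cap, 97% with a pilot-matched beta-binomial.

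**5. If the wider workforce has lower support than the pilot.** Beta-binomial, SD 3.21, assumed means 24, 26 and 28: rejection in 46%, 89% and 100%.

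**6. Does the mean need replacing?** In the pilot-matched support shapes the 95% interval for the mean covers 93.7% (beta-binomial) and 94.6% (censored normal), with average half-widths of 0.630 and 0.634. In the rounded, capped shapes of step 4, coverage is 94.3% (latitude), 95.1% (demand) and 95.2% (support). Coverage fell clearly only in a constructed case with about 2% of scores at the minimum of 8, to about 86%.

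**The case against.** The strongest reply is that 3.3 contains a conventional descriptive sentence, not a mechanical gate. It states no rule that a p-value below 0.05 means median only, and it does not forbid giving the mean as well. The primary analysis is mainly descriptive. The regression and random-effects models give estimates on the mean scale whatever the normality test shows. The categorical analysis, with its ±5% accuracy and SUMER's four-category distribution, does not depend on normality. A full analysis plan may tabulate both summaries. All of this stands and limits the point to a minor one. It does not remove it, because the article states a data-dependent choice for its primary score and that choice does not match its own sizing.

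A reader might go further and infer that the support median will sit at the ceiling of 32, or 2.06 points above the mean. The documents do not support that. The pilot line reads "high social support (29.94 ± 3.21, 100% above 24". A pilot median of 32 is forced only if mean, SD and all scores at 25 or more are taken together. If a score of 24 is allowed, the median is 31 or 32. From mean and SD alone it can be as low as 29. In the rounded, capped simulation that yields the near-100% rejection, the median is about 30 and is essentially never 32. The pilot was also 19 physicians at one hospital, while the study recruits 120 workers of all emergency occupations. Assumed means of 24, 26 and 28 give medians of 24, 26 and 29.

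Nor does it follow that ±0.63 ceases to apply. It stays valid for the mean whenever the mean is reported. Comparison with SUMER would not become impossible either: the article gives no SUMER value for support, and in the rounded, capped shapes the median and mean of latitude and demand differ by less than 0.1 point.

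**Conclusion.** The point holds as a minor one. Section 3.3 leaves the summary of the primary scores, and the test of their change, to the observed distribution, while 3.1 justifies the sample by the precision of means and the SUMER demand and latitude values are means. At pilot values and n = 100, support would almost certainly fail Shapiro–Wilk, demand quite possibly (13% to 97% by assumed shape, about 70% when rounded and capped), and latitude in roughly one sample in five. Mixed summaries across dimensions or waves are therefore a realistic result of following the text literally.

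The conclusion rests on items coded 1 to 4, on Shapiro–Wilk at 0.05 (3.3 sets 0.05 for its tests but no cut-off for this choice), and on assumed score shapes. The near-certain rejection for support also needs the pilot mean to carry over approximately.

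**What to change.** In 3.3, replace the conditional rule for the Karasek scores with two sentences:

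- For all three dimensions, at every wave, report mean, SD and 95% CI whatever the normality test shows, with median and IQR in addition.
- For the change between the control day and the end of the night session, report the paired mean difference with 95% CI (paired t-test or mixed model) as the main analysis in all three dimensions, with Wilcoxon as a sensitivity analysis.

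This ties the reported result to the margins and detectable differences in 3.1 and puts every wave on one scale. It needs no extra data or resources.
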